### Patient diary

The patients will complete a diary consisting of four parts; 1) Pain at rest is measured four times daily using an 11-point box Numeric Ranking Scale (NRS). The NRS has been found a reliable, valid and a responsive tool in geriatric patients[63]. 2) Consumption of painkillers. Type, dosage and frequency of pain killers will be recorded. This is recommended in recent evidence-based guidelines for management of hip and knee OA[64] 3) The need for continuous cane use and 4) Completing the HOOS-pain questionnaire. The diary will be filled in each day for the first five days and then every second week until 3 months after surgery.

Digital scanning will be used for questionnaires, and manual double data entry will be done[65].

### Assessments and follow-up period

Assessments point is presented in Table 2. A reminder will be sent per SMS on all the selected days for follow-up. The patients will receive the first set of questionnaires at the outpatient clinic at baseline. The following three sets, including return envelopes, will be handed out during the in-hospital stay. Furthermore, a reminder will be send per SMS at three, six and twelve months. In case of missing return, a new set and a reminder to complete the questionnaires will be sent by ordinary post service. All questionnaires will be completed at the patients’ home. In case of missing visits for physical function test or assessment in the gait laboratory, the patient will be contacted by phone, and a new appointment will be scheduled.

**Table 2 Tab2:** **Outcomes and assessment points**

		Assessments point			
Primary outcome	Data collection instrument (unit)	Baseline	Post (days)	Post (weeks)	Post (months)
Function of daily living	HOOS-PS	Pre			3, 6, 12
Secondary outcomes					
Patient reported outcomes					
Pain	HOOS-pain	Pre			3, 6, 12
Quality of life	HOOS-QoL	Pre			3, 6, 12
Physical activity	UCLA	Pre			3, 6, 12
General health	EQ-5D	Pre			3, 6, 12
Limping	Harris Hip Score	Pre			3, 6, 12
Explorative outcomes					
Pain					
Pain	HOOS-pain	Pre	5	2- 10	3
Use of medication	(type, quantity)	Pre	1- 5	2- 10	3
Short term pain measure	NRS	Before and after each test (pre- 12 months)			
Physical function					
20 Meter Walk test (20WT)	Stopwatch (s and steps)	Pre	3	3	3
Timed Up and Go test (TUG)	Stopwatch (s)	Pre	3	3	3
Chair Stand - test (30s-CST)	(quantity)	Pre	3	3	3
Knee Bend test (30s-knee bend)	(quantity)	Pre	3	3	3
Trendelenburg test	(positive/negative)	Pre			3
Joint mobility (Hip ROM)	Goniometer (degrees)	Pre			3
Data from 3D-gait analysis					
Total score for kinematic data	GDI (points)	Pre			3, 12
EMG	(frequency and amplitude)	Pre			3, 12
Hip Muscle strength	MVC (Nm/kg)	Pre			3, 12
Rate of forced development	0-200 ms MVC (Nm)	Pre			3, 12

### Adverse events

A medical record audit will be performed at twelve months post-surgery. Adverse events regarding periprosthetic fracture, nerve palsy, wound infection, deep thrombosis or pulmonary embolism, dislocation and revisions will be collected. Pain will be assessed before and after all sessions of physical function test, gait-analysis and MVC measurements. Pain >5 on the NRS is considered an event that may influence the patients’ effort of maximal performance. The assessment of pain will provide information about the feasibility of the test battery. No interim analysis or stopping guidelines are planned. Both interventions are well known and routinely performed with few severe adverse effects. However; we will register and report any adverse events to the appropriate health authorities.

### Sample size

Sample size calculation was performed upon the primary outcome HOOS-PS, using one preoperative and three follow-up assessments and an estimated correlation between follow-up measurements of 0.5. We considered a minimal important difference of 10 points between the two groups at 12 months follow-up to be of clinical relevance[66–69] and used a standard deviation of 16.7 and 16.1 postoperatively[24]. We have performed our sample size calculation using the function "sampsi method(change)" supported by the Stata 13 software and described by Frison and Pocook[70]. To achieve a statistical power of 80% (β = 0.80), it was calculated that a sample size of n = 29 was needed in each intervention group in order to detect statistical significant differences at α = 0.05 level. N = 40 was used to account for possible drop-outs. A secondary sample size estimation was conducted to estimate the number of patients needed for analysing the primary explorative GDI. We had á prior defined that a clinically relevant improvement in gait function measured in GDI is 7.5 point, which corresponds to half a standard deviation in the only available randomised clinical trial using GDI as outcome measure[71]. From data collected in our own gait laboratory we know that the standard deviation in hip OA-patients is 9 point preoperatively[72]. To achieve a statistical power of 80% (β = 0.80), it was calculated that a sample size of n = 17 was needed in each intervention group in order to detect statistical significant differences at α =0.05 level. Sample size in each group on n = 20 was used to account for possible drop-outs.

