### Primary outcome

#### Physical function

Hip Disability and Osteoarthritis Outcome Score (HOOS 2.0), subscale "Physical Function Short form (HOOS-PS)", will be used as the primary outcome, with primary endpoint after twelve months. The subscale HOOS-PS is an aggregation and shortening of the two original subscales of HOOS-ADL and Sport and Recreation. It has been developed to optimize the measurement of physical function and at the same time lower the burden of long questionnaires for the patients. The HOOS-PS subscale includes five items (three from HOOS-ADL and two from HOOS sport and recreation) that cover a wide range of physical functions, from low demand to high demand functions[21] It is a disease-specific patient-reported outcome measure developed to assess the patients’ opinion about their hip associated problems[22–24]. The subscale ranges from 0 point (extreme symptoms) to 100 point (no symptoms). HOOS-PS has been evaluated regarding validity and responsiveness in THR patients. HOOS-PS was found to have high internal consistency and responsiveness[24]. HOOS 2.0 has been evaluated regarding validity and reliability in THR patients. It was found to have high content validity, construct validity, test-retest reliability, responsiveness and interpretability[22]. One study also found good internal consistency and little floor and ceiling effect[25]. All items of HOOS 2.0 has been translated into Danish[26].

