### Statistical analysis

Baseline characteristic of study participants, will be presented with mean and SD, for all relevant outcomes, according to CONSORT item 15[19]. The primary statistical analysis will be performed between the two groups on mean change in HOOS-PS from baseline to twelve months follow-up. To evaluate the treatment effect (mean difference between the groups at three, six and twelve months), we will employ a random effect mixed linear model analysis (repeated measures) with point estimates[73]. This model includes the interaction between treatment and elapsed time, adjusted for baseline values and assuming that data is missing completely at random (MCAR)[73]. Model assumptions will be checked by residual plots. The secondary statistical analysis will include the same approach as described above for all the secondary outcomes. We will present the results with mean and standard deviation for both baseline and follow-up measurements in the two groups. Furthermore we will present the adjusted difference in mean between the groups at 12 months including 95% CI. Finally, the effect size using Cohen’s *d* effect size with indexes for small, medium and large effect as proposed by Cohen, 1992 will be reported[74]. The intention-to-treat (ITT) principle will be applied[75]. Subsequent per-protocol analysis may be needed in case a substantial number of data is lost during follow-up. All data will be checked for Gaussian distribution, and parametric statistics will be used were appropriate. An α-level of 0.05 will be used, and data presented as means with 95 CI, unless otherwise stated. Finally, the number needed to treat (NNT) for a positive effect of treatment (>10 points on HOOS-PS) will be analysed. All statistical analyses will be blinded and performed using Stata 13 software (StataCorp, Texas, USA).

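### The 29 per group for 80% power is sized for the mean of three follow-up visits, while the primary effect is the baseline-adjusted 12-month difference, which needs about 32

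*Protocol article*

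**What the plan says.** In the Protocol article, Sample size, the HOOS-PS calculation is described as "using one preoperative and three follow-up assessments and an estimated correlation between follow-up measurements of 0.5". The target effect is tied to one visit: "We considered a minimal important difference of 10 points between the two groups at 12 months follow-up to be of clinical relevance". For the spread, the authors "used a standard deviation of 16.7 and 16.1 postoperatively". The software routine named is the change option of Stata's sampsi command. The result is 29 per group for 80% power at α = 0.05, raised to 40 per group for drop-outs. Power of 80% is glossed there as β = 0.80.

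Under Primary outcome, HOOS-PS "will be used as the primary outcome, with primary endpoint after twelve months".

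The Statistical analysis section opens with "The primary statistical analysis will be performed between the two groups on mean change in HOOS-PS from baseline to twelve months follow-up". It then specifies a repeated-measures mixed model: "This model includes the interaction between treatment and elapsed time, adjusted for baseline values". Of the result it says "we will present the adjusted difference in mean between the groups at 12 months including 95% CI".

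**The concern.** With one baseline and three follow-up measurements, the change method compares the groups on the mean of the three follow-ups minus baseline. Averaging three scores correlated at 0.5 reduces the variance, so fewer patients are needed than for any single visit. The plan, however, does not average the visits. Its interaction term gives each visit its own treatment effect, and the effect of interest is the one at 12 months.

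The stated 80% power at 29 evaluable patients would therefore belong to a quantity that the trial does not report as its primary result. The allowance between 40 randomised and 29 needed would look wider than it is. A second difficulty is that the calculation depends on the correlation between baseline and follow-up, and the section gives a correlation only between follow-ups.

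**Working it through.** **Inputs (Protocol article, Sample size).** Difference 10 points. SDs 16.7 and 16.1, taken as the two groups' SDs and applied at every visit. One baseline and three follow-ups. Correlation between follow-ups 0.5. α = 0.05, taken as two-sided. Power 80%. The baseline/follow-up correlation r is not stated and is assumed to be 0.5 at first.

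**Formula.** n per group = (1.960 + 0.842)² × (16.7² + 16.1²) × f / 10², where f is the variance factor of the contrast. The sum of variances is 278.89 + 259.21 = 538.10, so n = 7.849 × 538.10 × f / 100 = 42.23 × f. Power at n is Φ(10 / √(538.10 × f / n) − 1.960).

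**Step 1: reproduce 29.** Mean of three follow-ups minus baseline: f = (1 + 2 × 0.5)/3 + 1 − 2 × 0.5 = 0.667. Then n = 42.23 × 0.667 = 28.2, rounded up to 29 (power 81% at 29). The stated figure is reproduced. Other versions with the same inputs give different answers: the same contrast one-sided gives 23, and baseline adjustment of the three-visit mean (f = 0.667 − 0.25 = 0.417) gives 18. The three-visit mean without baseline also has f = 0.667 and gives 29, but it is still an average over visits.

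**Step 2: the planned contrast.** Baseline-adjusted difference at 12 months: f = 1 − r² = 1 − 0.25 = 0.75. Then n = 42.23 × 0.75 = 31.7, rounded up to 32.
- At 29: 10 / √(538.10 × 0.75 / 29) − 1.960 = 2.681 − 1.960 = 0.721, power 76%.
- At 40: 10 / √(538.10 × 0.75 / 40) − 1.960 = 3.148 − 1.960 = 1.188, power 88%.

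**Step 3: do the earlier visits help?** With complete data and a separate effect per visit, they should add essentially nothing to the 12-month effect. A simulation of the model (4,000 trials per size, all correlations 0.5, covariance taken as known) gave 75% power at 29 and 88% at 40, in line with Step 2.

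**Step 4: drop-out margin.** 40 down to 29 is 11/40 = 27.5%. 40 down to 32 is 8/40 = 20%.

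**Step 5: sensitivity to the unstated correlation (assumed range).**

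| Baseline/12-month r | f = 1 − r² | n per group | Power at 29 | Power at 40 | Loss from 40 that leaves n |
|---|---|---|---|---|---|
| 0.3 | 0.91 | 39 | 68% | 82% | 2.5% |
| 0.4 | 0.84 | 36 | 72% | 84% | 10% |
| 0.5 | 0.75 | 32 | 76% | 88% | 20% |
| 0.6 | 0.64 | 28 | 83% | 93% | 30% |

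The shortfall at 29 vanishes when 1 − r² ≤ 29/42.23 = 0.687, that is, when r is about 0.56 or more.

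**Step 6: conditional reading.** If the primary comparison were an unadjusted change score from baseline to 12 months, then f = 2 × (1 − 0.5) = 1.0 and n = 42.2, rounded up to 43. Power would be 64% at 29 and 78% at 40.

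**The case against.** The strongest reply is that the trial enrols 40 per group, not 29, and that the planned model has about 88% power at 40 if r = 0.5. This stands. A reader might infer from the mismatch that the trial as enrolled is underpowered. The documents do not support that for the adjusted analysis: even at r = 0.3, power is 82% at 40 with no loss.

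A reader might also infer from the words on mean change that the primary test is an unadjusted change score, so that even 40 per group falls short. The Statistical analysis section never says unadjusted. It goes on to a model with baseline adjustment and reports the adjusted 12-month difference. With baseline as a covariate, analysing change or the follow-up score gives the same treatment estimate. The figures in Step 6 therefore apply only under a looser reading of that sentence.

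Third, it is an inference that the authors used 0.5 for the baseline/follow-up correlation. The value reproduces 29, but so does a calculation on the follow-up mean alone. A true correlation of 0.6 would give 83% power at 29. That concerns the power obtained and does not rescue the planning calculation: the change method with 0.6 would have returned 20, not 29.

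Fourth, the protocol states no tolerated loss; 27.5% is only what 40 and 29 imply. Patients who miss the 12-month visit but have earlier scores also contribute something to a mixed model. If 29 of 40 are seen at 12 months and all 40 earlier, then at r = 0.5 the effective f/n is 0.625/29 + 0.125/40 = 0.0247, against 0.75/29 = 0.0259, and power is about 78% instead of 76%. The gain is real but small.

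**Conclusion.** The mismatch holds and its size is moderate. The arithmetic is correct for the method named, but that method targets the mean over follow-up, whereas the outcome section, the 10-point difference and the analysis model all point to 12 months. For the baseline-adjusted 12-month difference the requirement is about 32 per group, with power of about 76% at 29 and 88% at 40. The margin for loss at 12 months is about 20%. These figures rest on the protocol's SDs applying at every visit, two-sided testing, and an assumed baseline/12-month correlation of 0.5. Over 0.3 to 0.6 the requirement runs from 39 to 28 per group and power at 29 from 68% to 83%.

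This should be fixed, because the stated power describes a different quantity. It does not show that the planned enrolment is inadequate.

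**What to change.** - In Statistical analysis, state that the primary estimate is the baseline-adjusted 12-month difference in HOOS-PS from the mixed model, and reword the sentence on mean change so that it cannot be read as a separate unadjusted test.
- In Sample size, restate the number needed and the power for that estimate: about 32 per group at r = 0.5, 88% power at 40, and 80% power kept up to about 20% loss at 12 months. Give the baseline/12-month correlation used, its source, and results over a range such as 0.3 to 0.6.
- Correct β = 0.80 to β = 0.20.

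The cost is rewording two paragraphs. No extra patients are needed; the stated power and drop-out margin become slightly less favourable.

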### Randomisation

Balanced 1:1 block randomisation was performed using a computer-generated list containing a sequence of one letter and one number; "A" referring the patient to posterior approach, "B" referring the patient to lateral approach. "1" referring the patient to participate in the gait analysis and thus contributing with data on GDI, and "0" referring the patient not to participate in the gait analysis (Figure 1). Four blocks of 20 patients each was generated. The sequence was generated by a third person (JL) not involved in the trial. The letter and number combination was written on paper, folded and placed in sealed opaque consecutively numbered envelopes. The booking secretary will open the envelopes in the given order, and according to the content the patient will be scheduled for operation. In the first three blocks there will be a 66% chance of being allocated to group 1(gait analysis). This will enable us to verify the sample size calculation of 2x20 patients for the GDI. A recompilation will be made, based on ungrouped results of GDI for the 20 first actual gait analyses performed. From this, we will adjust the final number of patients allocated to gait analysis accordingly.

**Figure 1 Fig1:**
[figure not shown]
**Study flow chart.**

### Blinding

The patients will be blinded to treatment. The patients are told prior to participation that they will not be informed about the type of intervention and they are carefully explained the reasons for this. Also the health care providers (doctors, nurses and physiotherapists) are all explained the importance of not talking about the intervention with the patients, and since the patients post operatively are treated after the same rehabilitations protocol, there is no need to discuss interventions. Blinding to treatment allocation (surgeons, ward nurses and, physiotherapists) is not possible due to the nature of the intervention. However, the data collectors (except one ([name]) performing gait analysis) and the principal investigator (SR) analysing the data will be blinded throughout the trial. We will use recoded identification numbers when analysing the data. The recoding will be performed by an independent person (JL).

### Statistical analysis

Baseline characteristic of study participants, will be presented with mean and SD, for all relevant outcomes, according to CONSORT item 15[19]. The primary statistical analysis will be performed between the two groups on mean change in HOOS-PS from baseline to twelve months follow-up. To evaluate the treatment effect (mean difference between the groups at three, six and twelve months), we will employ a random effect mixed linear model analysis (repeated measures) with point estimates[73]. This model includes the interaction between treatment and elapsed time, adjusted for baseline values and assuming that data is missing completely at random (MCAR)[73]. Model assumptions will be checked by residual plots. The secondary statistical analysis will include the same approach as described above for all the secondary outcomes. We will present the results with mean and standard deviation for both baseline and follow-up measurements in the two groups. Furthermore we will present the adjusted difference in mean between the groups at 12 months including 95% CI. Finally, the effect size using Cohen’s *d* effect size with indexes for small, medium and large effect as proposed by Cohen, 1992 will be reported[74]. The intention-to-treat (ITT) principle will be applied[75]. Subsequent per-protocol analysis may be needed in case a substantial number of data is lost during follow-up. All data will be checked for Gaussian distribution, and parametric statistics will be used were appropriate. An α-level of 0.05 will be used, and data presented as means with 95 CI, unless otherwise stated. Finally, the number needed to treat (NNT) for a positive effect of treatment (>10 points on HOOS-PS) will be analysed. All statistical analyses will be blinded and performed using Stata 13 software (StataCorp, Texas, USA).

### Ethics

The trial complies with the Declaration of Helsinki. It is approved by the Danish Data Protection Agency and The Danish Regional Committee on Biomedical Research Ethics (Southern Denmark), Project-ID S-20120009. A written and orally informed consent will be collected prior to inclusion of all participants.

## Discussion

The choice of surgical approach and the influence on patient-reported outcome, physical function, hip muscle function and gait are often debated. Especially, the lateral approach and its impact on the hip abductor muscles are a concern that may be associated with decreased PROM, reduced physical function and increased limping. Interest in reducing the surgical induced muscle damaged is also emphasised by a study showing that decreased lower limb muscle strength is associated with deterioration of ADL functions[76]. Despite this, only few studies have evaluated PROM, physical function and gait between the PA group and LA group.

### PROM

The trial focuses on HOOS-PS as primary outcome after twelve months, along with a number of secondary outcomes, in order to evaluate the patients’ perspective on physical function (HHS-limping), physical activity (UCLA), pain (HOOS-Pain, EQ-5D) and quality of life (HOOS-QoL, EQ-5D). All of these are valid measurements and recommended for use in RCTs[77].

To our knowledge, only three studies have investigated PROM when comparing PA with LA[6, 11, 18]. Of these only one study is a randomised controlled trial (RCT) and did not use PROM as primary outcome. Furthermore, the three studies do not agree in their conclusions of which approach is superior in terms of patient reported physical function and pain. The two non-randomised cohort studies are demonstrating a small, but significant, difference in favour of PA. Contrary, the RCT did not find any differences in WOMAC, which was evaluated as a secondary outcome. Also, two studies have compared the PA with LA using Harris Hip Score (HHS)[12, 18]; however, HHS is not entirely patient-reported. The first study found that LA had a significant inferior outcome on total HHS after twelve months[12], whereas the other study found no differences after three months[18].

PROM is recommended by OMERACT (Outcome Measures in Rheumatologic Clinical Trials) as the core set of outcome measures in phase III clinical trials investigating OA treatment, including THR[77]. The core set outcome includes pain, physical function and patient global assessment. We have chosen the HOOS-PS as primary outcome for mainly three reasons. First, physical function has been defined by OMERACT as one out of three core set outcomes to evaluate. Physical function is well reflected in HOOS-PS, which includes 5 items. Second, we find it relevant to use HOOS-PS as primary outcome, because it reflects the possible negative influence of LA due to the surgical damage on the hip abductor muscles, which could lead to reduced physical function for these patients. Third, HOOS is in a recent review recommended for evaluation of THR patients, because it was found to be the best validated and a reliable PROM when compared with other commonly used PROMs (WOMAC, OHS, modified HHS etc.)[22].

Pain is also a core set outcome in the OMERACT guidelines[77]. Measurements of pain are represented in both the secondary and the explorative outcomes, by HOOS-pain, NRS and actual intake of painkillers. Lastly, a global patient assessment score is the third core set outcome in the OMERACT guidelines, and it will be measured by the patients’ perception of their overall health with the second part of EQ-5D. The use of a specific question regarding limping from HHS will provide important information on the gait quality perceived by the patients and will be further explored using GDI.

